### Sample size

The sample size for the trial was to recruit 3300 children (1100 per treatment arm) in order to have 80% power to detect a two-point difference in Bayley III composite cognitive score between the iron supplementation and placebo arm and the MNPs and placebo arm (two-sided 2.5% level of significance per comparison), assuming a standard deviation of 15 and a 20% loss to follow up after 3 months of intervention. No interim analyses to stop the trial early were planned, and no interim analysis was conducted.

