### General principles

The intention-to-treat population will be used for the analysis of all primary, key secondary, secondary, and exploratory outcomes and will include all children who were randomised. In case of missing outcome data, we will follow the missing data handling strategy outlined below. The safety population will be used for the analysis of all safety outcomes and consists of all children who received at least one study treatment (including control). Children who have withdrawn informed consent for use of all their data will be excluded from all analyses. Children will be reported and analysed according to their randomised treatment allocation. Time-windows will be applied to all visit-wise data collected at baseline, month 3, and month 12, with assessments outside the predefined visit windows excluded from the analyses. Outcomes will be summarised using frequencies and percentages (based on the non-missing sample size) for categorical variables, mean and standard deviation for continuous variables, or median and quartiles (25th and 75th percentile) for non-symmetrical continuous variables. All analyses models will be adjusted for the stratification variables used during the randomisation (union and sex). All confidence intervals and P-Values will be two-sided.

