Change in haemoglobin concentration (g/L)	XXXX	X.X (X.X)	XXXX	X.X (X.X)	XXXX	X.X (X.X)	X.X (X.X to X.X)	0.XXX	0.XXX	X.X (X.X to X.X)	0.XXX	0.XXX	X.X (X.X to X.X)	0.XXX	0.XXX
Ferritin (µg/L)	XXXX	XX.X (XX.X- XX.X)	XXXX	XX.X (XX.X- XX.X)	XXXX	XX.X (XX.X- XX.X)	X.XX (X.XX to X.XX)	0.XXX	0.XXX	X.XX (X.XX to X.XX)	0.XXX	0.XXX	X.XX (X.XX to X.XX)	0.XXX	0.XXX
Secondary variables															
Anthropometric indices															
Stunting	XXXX	XX (X.X%)	XXXX	XX (X.X%)	XXXX	XX (X.X%)	X.XX (X.XX to X.XX)			X.XX (X.XX to X.XX)			X.XX (X.XX to X.XX)		
Underweight	XXXX	XX (X.X%)	XXXX	XX (X.X%)	XXXX	XX (X.X%)	X.XX (X.XX to X.XX)			X.XX (X.XX to X.XX)			X.XX (X.XX to X.XX)		
Change in weight-for- lenght z-score	XXXX	X.X (X.X)	XXXX	X.X (X.X)	XXXX	X.X (X.X)	X.X (X.X to X.X)			X.X (X.X to X.X)			X.X (X.X to X.X)		
Wasting	XXXX	XX (X.X%)	XXXX	XX (X.X%)	XXXX	XX (X.X%)	X.XX (X.XX to X.XX)			X.XX (X.XX to X.XX)			X.XX (X.XX to X.XX)		
Change in head circumference	XXXX	X.X (X.X)	XXXX	X.X (X.X)	XXXX	X.X (X.X)	X.X (X.X to X.X)			X.X (X.X to X.X)			X.X (X.X to X.X)		
Laboratory indices															
Anaemia	XXXX	XX (X.X%)	XXXX	XX (X.X%)	XXXX	XX (X.X%)	X.XX (X.XX to X.XX)			X.XX (X.XX to X.XX)			X.XX (X.XX to X.XX)		
Iron deficient	XXXX	XX (X.X%)	XXXX	XX (X.X%)	XXXX	XX (X.X%)	X.XX (X.XX to X.XX)			X.XX (X.XX to X.XX)			X.XX (X.XX to X.XX)		
Iron deficient anaemia	XXXX	XX (X.X%)	XXXX	XX (X.X%)	XXXX	XX (X.X%)	X.XX (X.XX to X.XX)			X.XX (X.XX to X.XX)			X.XX (X.XX to X.XX)		

MNPs, multiple micronutrient powders; CI, confidence interval *Values are mean (SD) or no. (%), with the exception of ferritin which is median (25th to 75th percentile). †Multiplicity-adjusted according to the pre-specified multiple testing strategy.

Continuous key secondary, secondary, and exploratory outcomes will be analysed similarly as the primary outcome. Ferritin (µg/L) will be log
_e_ transformed before analysis. Binary outcomes will be analysed using a generalised linear mixed model with a log-link function and binomial distribution, including child as a random intercept. In case of non-convergence, we will use a logit link function instead.

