Cough/Difficulty breathing - total number of times reported	Intervention period	XX (X-XX)	XX (X-XX)	XX (X-XX)	X.XX (X.XX to X.XX)	0.XXX	X.XX (X.XX to X.XX)	0.XXX	X.XX (X.XX to X.XX)	0.XXX
	Extended follow-up period	X (X-X)	X (X-X)	X (X-X)	X.XX (X.XX to X.XX)	0.XXX	X.XX (X.XX to X.XX)	0.XXX	X.XX (X.XX to X.XX)	0.XXX
	Study period	XX (X-XX)	XX (X-XX)	XX (X-XX)	X.XX (X.XX to X.XX)	0.XXX	X.XX (X.XX to X.XX)	0.XXX	X.XX (X.XX to X.XX)	0.XXX

MNPs, multiple micronutrient powders; CI, confidence interval Intervention period – 0–3 months, Extended follow-up period 4–12 months, Study period 0–12 months. *Values are median (25th to 75th percentile). †Ratio is incidence rate ratio.

The number and percentage of children who died, had at least one (overnight) hospitalisation, reported at least one serious adverse event, and had at least one clinic visit (due to any infection, fever, diarrhoea, bloody stool, vomiting, cough/ difficulty breathing, other infection) during the intervention period, extended follow-up period, and study period will be reported and compared between treatments using a log-binomial regression model (
Table 4). 

**Table 4. T4:** Death, serious adverse events, hospitalisation, according to treatment group (safety population).

	Period		Iron (N=XXXX)	MNPs (N=XXXX)	Placebo (N=XXXX)	P-Value Iron vs. Placebo	P-Value MNPs vs. Placebo	P-Value Iron vs. MNPs
Children who died - no. (%)								
	Intervention period		XXX (XX.X)	XXX (XX.X)	XXX (XX.X)	0.XXX	0.XXX	0.XXX
	Extented follow-up period		XXX (XX.X)	XXX (XX.X)	XXX (XX.X)	0.XXX	0.XXX	0.XXX
	Study period		XXX (XX.X)	XXX (XX.X)	XXX (XX.X)	0.XXX	0.XXX	0.XXX
Children ≥1 hospitalisation * - no. (%)								
	Intervention period		XXX (XX.X)	XXX (XX.X)	XXX (XX.X)	0.XXX	0.XXX	0.XXX
	Extended follow-up period		XXX (XX.X)	XXX (XX.X)	XXX (XX.X)	0.XXX	0.XXX	0.XXX
	Study period		XXX (XX.X)	XXX (XX.X)	XXX (XX.X)	0.XXX	0.XXX	0.XXX
Children with ≥1 SAE - no. (%)								
	Intervention period		XXX (XX.X)	XXX (XX.X)	XXX (XX.X)	0.XXX	0.XXX	0.XXX
	Extented follow-up period		XXX (XX.X)	XXX (XX.X)	XXX (XX.X)	0.XXX	0.XXX	0.XXX
	Study period		XXX (XX.X)	XXX (XX.X)	XXX (XX.X)	0.XXX	0.XXX	0.XXX
Children ≥1 clinic visit † - no. (%)								
	Intervention period							
		Any reason	XXX (XX.X)	XXX (XX.X)	XXX (XX.X)	0.XXX	0.XXX	0.XXX
		Due to fever	XXX (XX.X)	XXX (XX.X)	XXX (XX.X)	0.XXX	0.XXX	0.XXX
		Due to diarrhea	XXX (XX.X)	XXX (XX.X)	XXX (XX.X)	0.XXX	0.XXX	0.XXX

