		Due to bloody stool	XXX (XX.X)	XXX (XX.X)	XXX (XX.X)	0.XXX	0.XXX	0.XXX
		Due to vomiting	XXX (XX.X)	XXX (XX.X)	XXX (XX.X)	0.XXX	0.XXX	0.XXX
		Due to cough/ difficulty breathing	XXX (XX.X)	XXX (XX.X)	XXX (XX.X)	0.XXX	0.XXX	0.XXX
		Due to other ‡	XXX (XX.X)	XXX (XX.X)	XXX (XX.X)	0.XXX	0.XXX	0.XXX
	Extended follow-up period							
		Any reason	XXX (XX.X)	XXX (XX.X)	XXX (XX.X)	0.XXX	0.XXX	0.XXX
		Due to fever	XXX (XX.X)	XXX (XX.X)	XXX (XX.X)	0.XXX	0.XXX	0.XXX
		Due to diarrhea	XXX (XX.X)	XXX (XX.X)	XXX (XX.X)	0.XXX	0.XXX	0.XXX
		Due to bloody stool	XXX (XX.X)	XXX (XX.X)	XXX (XX.X)	0.XXX	0.XXX	0.XXX
		Due to vomiting	XXX (XX.X)	XXX (XX.X)	XXX (XX.X)	0.XXX	0.XXX	0.XXX
		Due to cough/ difficulty breathing	XXX (XX.X)	XXX (XX.X)	XXX (XX.X)	0.XXX	0.XXX	0.XXX
		Due to other ‡	XXX (XX.X)	XXX (XX.X)	XXX (XX.X)	0.XXX	0.XXX	0.XXX
	Study period							
		Any reason	XXX (XX.X)	XXX (XX.X)	XXX (XX.X)	0.XXX	0.XXX	0.XXX
		Due to fever	XXX (XX.X)	XXX (XX.X)	XXX (XX.X)	0.XXX	0.XXX	0.XXX
		Due to diarrhea	XXX (XX.X)	XXX (XX.X)	XXX (XX.X)	0.XXX	0.XXX	0.XXX
		Due to bloody stool	XXX (XX.X)	XXX (XX.X)	XXX (XX.X)	0.XXX	0.XXX	0.XXX
		Due to vomiting	XXX (XX.X)	XXX (XX.X)	XXX (XX.X)	0.XXX	0.XXX	0.XXX
		Due to cough/ difficulty breathing	XXX (XX.X)	XXX (XX.X)	XXX (XX.X)	0.XXX	0.XXX	0.XXX
		Due to other ‡	XXX (XX.X)	XXX (XX.X)	XXX (XX.X)	0.XXX	0.XXX	0.XXX

MNPs, multiple micronutrient powders; SAE, serious adverse event. Intervention period – 0–3 months, Extended follow-up period 4–12 months, Study period 0–12 months. *Hospitalisation is defined as an overnight stay. †Clinic visit is defined as visit to the clinic not resulting in hospitalisation. ‡Other is defined as stool with mucous, runny nose, skin problem, eye problem, oral problem, ear problem, constipation, check up, other.

C-reactive protein levels will be analysed using similar models as those described for the primary outcome and for inflammation similar models to those described for the binary key secondary and secondary outcomes.

We will present the multiplicity unadjusted P-Values for the safety outcomes, no multiple testing adjustment is planned.

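### Table 4 gives no effect estimate or interval for deaths, SAEs, hospitalisations or clinic visits, and its log-binomial model gives a Wald P near 1 when an arm has no events

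*SAP article*

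**What the plan says.** The section Safety outcomes: analysis sets one method for every row and period of Table 4. Deaths, overnight hospitalisations, SAEs and clinic visits by reason "will be reported and compared between treatments using a log-binomial regression model". The periods are the intervention (months 0–3), extended follow-up (months 4–12) and the whole study.

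The shell of Table 4 has a count and percentage for each arm, then three comparison columns, of which the first is headed "P-Value Iron vs. Placebo". There is no column for an effect estimate or an interval. The same section adds: "We will present the multiplicity unadjusted P-Values for the safety outcomes, no multiple testing adjustment is planned". General principles says that "All confidence intervals and P-Values will be two-sided" and that all models are adjusted for union and sex. It does not say whether P-values come from a Wald or a likelihood-ratio test.

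Other tables are fuller. Table 3 (infectious morbidity) gives an incidence rate ratio with 95% CI beside each P-value. Table 2 gives an estimate with CI, and no P-value, for binary secondary outcomes such as stunting and anaemia.

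The only fallback for a binary model is in the section on efficacy outcomes: "In case of non-convergence, we will use a logit link function instead". It is written for the generalised linear mixed model used there.

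**The concern.** There are two linked problems.

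First, the gravest harms get the least informative comparison. The Discussion says that robust evidence on the possible risks of iron is lacking and expects the results to influence global policy. The question for these rows is how large an excess risk remains compatible with the data. A P-value does not answer it. The fitted model produces a ratio and an interval, but the table leaves them out.

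Second, a log-binomial model has no finite estimate of the risk ratio when one arm has no events. Default Wald output then gives a P-value close to 1 however many events the other arm has. Deaths are where this is most likely to arise and where a misleading P-value does most damage.

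**Working it through.** **Inputs.** Arm size is 1100 (SAP article, Sample size). The safety population is taken as about the same size, which is an assumption. The SAP gives no event rates for Table 4, so all event counts and risks below are assumptions, and there is no stated figure to reproduce.

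**Step 1: the model with an empty arm.** A binomial GLM with log link was fitted to 6 v 0 events (iron v placebo).
- Wald: log risk ratio 21.69, SE about 12,700, so z = 21.69 / 12,700 = 0.0017 and P = 0.999. The software reported convergence.
- Likelihood ratio: 2 × [6 ln(6/1100) + 1094 ln(1094/1100) − 6 ln(6/2200) − 2194 ln(2194/2200)] = 8.33 on 1 df, P = 0.004.
- Fisher, two-sided: 2 × (1100/2200) × (1099/2199) × … × (1095/2195) = 0.031.

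**Step 2: other counts.**

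| Iron v placebo | Wald P | Likelihood-ratio P | Fisher P |
|---|---|---|---|
| 3 v 0 | 0.999 | 0.041 | 0.250 |
| 5 v 0 | 0.999 | 0.008 | 0.062 |
| 6 v 0 | 0.999 | 0.004 | 0.031 |
| 8 v 0 | 0.999 | 0.0009 | 0.008 |
| 12 v 0 | 0.999 | <0.0001 | 0.0005 |
| 8 v 1 | 0.050 | 0.013 | 0.039 |

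The Wald P does not respond to the size of the imbalance while one arm is empty. With a single placebo event the model works again. At 3 v 0 the likelihood-ratio test gives 0.041 and the exact test 0.250, so naming the likelihood-ratio test alone would not settle the matter.

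**Step 3: does adjustment or the logit fallback change this?** With union and sex in the model, the Wald P stays at 0.999 for 6, 8 and 12 v 0, and convergence is again reported. With a logit link and the same terms, P is 0.999 for each. A rule tied to non-convergence would not be triggered, and the logit link would not help if it were.

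**Step 4: how likely is an empty arm?** For a common risk p, the chance that one arm is empty is q = (1 − p)^1100, and the chance that at least one of three is empty is 1 − (1 − q)³. For p = 0.1%, q = 0.333 and 1 − 0.667³ = 0.70.

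| Assumed risk in the period | Expected events per arm | Chance of at least one empty arm |
|---|---|---|
| 0.05% | 0.55 | 92% |
| 0.1% | 1.1 | 70% |
| 0.2% | 2.2 | 30% |
| 0.3% | 3.3 | 11% |
| 0.5% | 5.5 | 1% |
| 1% | 11 | about 0 |

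This is the chance that the breakdown occurs, not the chance that a harm is missed. Among the empty-arm counts in Step 2, the exact test first falls below 0.05 at 6 v 0.

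**The case against.** The best defence is that the table is not blank. Counts and percentages are printed for each arm, so a reader would see 6 v 0 deaths beside the P-value and could work out a crude risk difference. That stands. A reader might infer that the plan would hide an imbalance; it would not. What is missing is a printed estimate and interval, and the printed test could contradict the visible counts.

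A second defence is that P near 1 belongs to the Wald test and not to the log-binomial model as such. That also stands, since a likelihood-ratio test of the same fit gives 0.004 for 6 v 0. But the SAP names neither, so the result for deaths would depend on an unstated choice or a software default.

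Third, these P-values drive no decision rule, and the plan is still to be signed off at the blinded data review, where a sparse-event rule could be added. This limits the severity, and it is also the reason to raise the point now.

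Two stronger readings fail. A reader might infer that an empty union or sex level also spoils the treatment comparison. With assumed counts of 12, 6 and 3 (iron, MNPs, placebo), the adjusted iron-versus-placebo Wald P is 0.031 whether or not a union or a sex has no events; only the coefficient for the empty level diverges. A reader might also take the single N per column to mean that extended follow-up percentages include children already lost. The SAP does not say so. Table 3 has the same column header, and General principles bases percentages on the non-missing sample size. Any bias in the ratio would also need loss to differ between arms, and the SAP gives no such figures.

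**Conclusion.** The point holds in two parts.

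The missing estimate and interval in Table 4 can be read directly from the shell and rest on no assumption.

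The test failure is conditional. It needs an arm with no events and default Wald output. Under those conditions the P-value is about 0.999 for any imbalance, against 0.031 (Fisher) at 6 v 0 and 0.008 at 8 v 0. An empty arm is plausible for deaths, particularly in months 0–3, and for rare visit reasons such as bloody stool. It is unlikely for all SAEs or all hospitalisations if their risk is 0.5% or more. Adjustment for union and sex is not the cause, since the unadjusted model fails in the same way.

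This is a change that should be made, not a flaw that threatens the primary conclusion.

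**What to change.** Make both changes before the allocation code is broken. The SAP treats tracked changes made before then as planned, and changes after the signed version as post hoc.

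1. In Table 4, add a risk difference or risk ratio with two-sided 95% CI for each of the three comparisons, beside or in place of the P-value. Where an arm is empty, the raw risk ratio is zero or infinite, so use the risk difference or a penalised ratio.
2. For sparse rows, replace the Wald log-binomial test with an exact test (Fisher, or exact stratified by union and sex) or Firth-penalised regression, with an exact or profile-likelihood interval. State the trigger. It must cover at least any comparison with an empty arm; a threshold on the event count pooled over arms is better, because it can be applied while blinded.

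The cost is a few sentences, a revised table shell and slight extra analysis work. Exact tests are somewhat conservative. A plain Fisher test also drops the adjustment for union and sex that General principles requires, so either name it as an exception or use the stratified exact or Firth version.

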### Missing data handling

To describe the missing data, the frequency and percentage of children with missing data at baseline, month 3 and month 12 will be summarised for the child development, anthropometry, and laboratory outcomes. In addition, baseline and demographic characteristics will be summarized by those with and without missing data for the cognitive composite score (at baseline, month 3, and month 12) to explore the missing data assumption and identify any variables not included in the target analyses that are potentially associated with missingness (known as auxiliary variables).

As the primary strategy to handle missing data, the analysis will use a likelihood-based approach. This approach relies on the underlying assumption that the probability of missing outcome data is not related to the missing data but to some of the observed measured data in the model (Missing At Random [MAR]). 

As the secondary strategy (sensitivity analysis), missing data on the outcomes will be multiply imputed using chained equations. The imputation model will include union, sex, visit (categorical), the family care indicator total score (continuous), maternal education (continuous), all variables listed as specified for subgroup analyses, and it will be performed separately by treatment group. In addition, auxiliary variables identified during the blinded data review meeting may be included. The variables with missing data will be imputed using a linear regression model if continuous and logistic regression if binary, whereby ferritin will be log
_e_ transformed prior to imputation as this outcome will be log
_e_ transformed in the analysis of interest. The missing outcome data at baseline, 3-month and 12-month visits will be imputed using the “just another variable” approach (also known as imputing in wide format) which requires a separate imputation model for imputing the variable at each assessment time. The number of imputed data sets will be greater than or equal to the percentage of missing data in the available case analyses. The imputed data sets will be analysed using the models described. The estimates from the analyses of the imputed data sets will be combined to obtain a pooled common estimate and corresponding confidence interval using Rubin’s rules. For the above standard implementation of multiple imputation, we have assumed the outcome data are MAR.

### Adherence

Overall compliance across the 3-month intervention period will be derived as the total number of days the child has reported taking both the syrup and the sachet divided by the child’s study participation duration, with ‘complier’ defined as those with overall compliance ≥70%. If no data on treatment intake is available, compliance will be assumed to be 0%.

### Sensitivity analyses

In addition to the analyses specified for the primary, key secondary, and secondary outcomes, the following sensitivity analyses will be applied for these outcomes:

1. Analyses consisting of models adjusted for potential prognostic or predictive variables:

a. Adding to the model adjusted for union and sex, the main effect of family care indicator score (continuous) and maternal education (No education; 1–8 years schooling completed; 9–12 years schooling completed; >12 years schooling completed).b. Adding to the model adjusted for union and sex, the main effect of variables in
Table 1 demonstrating unexpected imbalance between the treatment arms after unblinding.c. Adding to the model adjusted for union and sex, the main effect for rater and the interaction between rater and study visit (only applies to Bayley III, Wolke’s Behaviour rating scale, and temperament questionnaire).d. Adding to the model adjusted for union, sex, family care indicator, and maternal education, the main effect for rater and the interaction between rater and study visit (only applies to Bayley III, Wolke’s Behaviour rating scale, and temperament questionnaire).

2. Analyses of the secondary strategy to handle missing data.

3. Analyses of the model adjusted for union and sex for the per-protocol population defined as randomised children who were compliant to treatment, and without protocol violations (no informed consent or withdrawn informed consent for use of all data, violation in/ exclusion criteria, or improper unblinding of the child’s allocated treatment).

4. Analyses using the Complier Average Causal Effect method to estimate the average effect of treatment among compliers
^
17
^.

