^, consisting of 33 questions each scored on a four-point scale with higher scores indicating a better temperament which will be grouped by summing into seven temperament summary scores.

Safety outcomes include infectious morbidity (includes fever, diarrhoea, bloody stool, vomiting, cough/ difficulty breathing), (serious) adverse events, and C-reactive protein (an inflammatory biomarker) and inflammation defined as C-reactive protein >5 mg/L.

Additional data collected included household baseline characteristics (union, religion, number of household members, parity, number of children under five years of age living in the household, maternal and paternal education, maternal and paternal occupation, wealth index
^
11
^, maternal depression
^
12,
13
^, household food insecurity
^
14
^) and child baseline characteristics (sex, age, currently breastfed, home stimulation as measured using the family care indicator score
^
15
^). Daily study medication intake was collected weekly during the 3-month intervention period and included reasons for non-adherence to the allocated treatment regimen. 

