### Efficacy (including selected laboratory) outcomes: analysis

A constrained longitudinal data analysis method proposed by Liang and Zeger
^
16
^ will be used to examine the primary outcome (Bayley III cognitive composite score at baseline, 3 months and 12 months post-baseline). The model will incorporate study visit as a categorical variable, treatment and treatment by study visit interaction and adjust for the stratification randomisation factors (union and sex) as main effects. The model will assume a common baseline mean across the three treatment arms and an unstructured variance-covariance among the repeated measurements. In case of non-convergence, we will consider alternative structures (first-order autoregressive, Toeplitz, compound symmetry). The treatment effect will be estimated from this model as the difference between two treatments in mean change from baseline to 3 months post-intervention (
Table 2).

**Table 2. T2:** Primary, key secondary, and secondary outcomes, according to treatment group (intention-to-treat population).

Assessment	Iron (N=XXXX)		MNPs (N=XXXX)		Placebo (N=XXXX)		Iron vs. Placebo			MNPs vs. Placebo			Iron vs. MNPs		
	no. of children measured	Mean (SD) *	no. of children measured	Mean (SD) *	no. of children measured	Mean (SD) *	Estimate (CI) †	P Value Unadjusted	P Value Adjusted †	Estimate (CI) †	P Value Unadjusted	P Value Adjusted †	Estimate (CI) †	P Value Unadjusted	P Value Adjusted †
Month 3															
Primary endpoint															
Bayley score															
Change in cognitive composite score	XXXX	X.X (X.X)	XXXX	X.X (X.X)	XXXX	X.X (X.X)	X.X (X.X to X.X)	0.XXX	0.XXX	X.X (X.X to X.X)	0.XXX	0.XXX	X.X (X.X to X.X)	0.XXX	0.XXX
Key secondary endpoints															
Bayley score															
Change in language composite score	XXXX	X.X (X.X)	XXXX	X.X (X.X)	XXXX	X.X (X.X)	X.X (X.X to X.X)	0.XXX	0.XXX	X.X (X.X to X.X)	0.XXX	0.XXX	X.X (X.X to X.X)	0.XXX	0.XXX
Change in motor composite score	XXXX	X.X (X.X)	XXXX	X.X (X.X)	XXXX	X.X (X.X)	X.X (X.X to X.X)	0.XXX	0.XXX	X.X (X.X to X.X)	0.XXX	0.XXX	X.X (X.X to X.X)	0.XXX	0.XXX
Anthropometric indices															
Change in length-for-age z-score	XXXX	X.X (X.X)	XXXX	X.X (X.X)	XXXX	X.X (X.X)	X.X (X.X to X.X)	0.XXX	0.XXX	X.X (X.X to X.X)	0.XXX	0.XXX	X.X (X.X to X.X)	0.XXX	0.XXX
Change in weight-for-age z-score	XXXX	X.X (X.X)	XXXX	X.X (X.X)	XXXX	X.X (X.X)	X.X (X.X to X.X)	0.XXX	0.XXX	X.X (X.X to X.X)	0.XXX	0.XXX	X.X (X.X to X.X)	0.XXX	0.XXX
Laboratory indices															

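### The per-protocol analysis selects children on adherence after randomisation but adjusts only for union and sex, so it could be biased if adherence works differently between arms (minor)

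*SAP article*

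**What the plan says.** All from the SAP article.

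- **Sensitivity analyses, item 3.** The per-protocol analysis is "Analyses of the model adjusted for union and sex for the per-protocol population defined as randomised children who were compliant to treatment". Children must also be free of listed protocol violations. It applies to the primary, key secondary and secondary outcomes.
- **Adherence.** Compliance is the share of days on which both syrup and sachet were reported taken. The threshold, in per cent, is given by "with ‘complier’ defined as those with overall compliance ≥70". For children without intake records the rule, also in per cent, is "If no data on treatment intake is available, compliance will be assumed to be 0", so they leave the per-protocol set.
- **Sensitivity analyses, item 1a.** Under the label of potential prognostic or predictive variables, a further model adds "the main effect of family care indicator score (continuous) and maternal education". Item 1d uses the same two variables together with rater. Item 3 does not carry them over.
- **Outcome variables.** Other family data are collected at baseline, among them "maternal and paternal education, maternal and paternal occupation, wealth index", maternal depression and household food insecurity.
- **Efficacy outcomes: analysis.** The longitudinal model includes the baseline score: "The model will assume a common baseline mean across the three treatment arms".
- **Sensitivity analyses, item 4.** The next item is "Analyses using the Complier Average Causal Effect method to estimate the average effect of treatment among compliers".

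**The concern.** Whether a child reaches 70% compliance is known only after treatment has started. Dropping the others means that the arms in the per-protocol set are no longer the groups that randomisation formed. A caregiver's education and the stimulation at home plausibly affect both whether the products are given and how the child develops. If they act on adherence differently by arm, or if adherence itself differs by arm, the adherers in one arm come from different homes from the adherers in another. Part of the per-protocol difference is then a difference between homes.

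The plan adjusts for family care indicator and maternal education in the full randomised set, where they are balanced in expectation, and leaves them out of the one regression model fitted to a set selected on adherence. The baseline score helps only in part. The constraint of one baseline mean for all arms is justified by randomisation and need not hold among adherers.

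What is at stake is the reading of a sensitivity analysis. A biased per-protocol estimate could seem to support or to question the primary result for reasons that have nothing to do with iron.

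**Working it through.** The plan states no figure on this point, so there is none to reproduce. The documents give neither adherence rates nor the link between home environment and score. The calculation is therefore an illustration with assumed inputs.

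**Inputs from the SAP article (Sample size).** SD 15; 1100 children per arm; 20% loss, so 1100 × 0.80 = 880 evaluable per arm; target difference 2 points; two-sided 2.5% per comparison.

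**Assumed inputs.** Half the children have low home stimulation. Given the baseline score, they score 4 points lower at month 3 (range 2 to 6). Non-adherence on placebo is 20% in the low group and 10% in the high group. On iron it is 40% in the low group (range 30% to 50%) and 10% in the high group. Loss to follow-up is taken as unrelated to adherence. There is no true treatment effect.

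**Share of low-stimulation homes among adherers**
- Placebo: 0.80 / (0.80 + 0.90) = 0.471
- Iron, central: 0.60 / (0.60 + 0.90) = 0.400
- Iron, low end: 0.70 / (0.70 + 0.90) = 0.4375
- Iron, high end: 0.50 / (0.50 + 0.90) = 0.357

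**Bias = (placebo share − iron share) × score gap**
- Central: (0.471 − 0.400) × 4 = 0.28 points, which is 14% of the 2-point target
- Low end: (0.471 − 0.4375) × 2 = 0.07 points
- High end: (0.471 − 0.357) × 6 = 0.68 points
- Same adherence pattern in both arms: the shares are equal and the bias is 0

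**Against the standard error.** SE = 15 × √(1/n₁ + 1/n₀), with n₀ = 0.85 × 880 = 748 placebo adherers.

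| Case | Iron adherers | SE | Bias / SE | Rejection of a true null at nominal 2.5% |
|---|---|---|---|---|
| Low end | 0.80 × 880 = 704 | 0.79 | 0.08 | 2.6% |
| Central | 0.75 × 880 = 660 | 0.80 | 0.35 | 3.4% |
| High end | 0.70 × 880 = 616 | 0.82 | 0.83 | 8.1% |

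The last column is 1 − Φ(2.241 − b/SE) + Φ(−2.241 − b/SE), where b is the bias. The SE takes no credit for the baseline score. A correlated baseline would lower it and so raise the ratios somewhat.

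**Second check, with a continuous family score.** Adherence follows a logistic model in a standardised family score, which is worth 1.5 to 4.5 points per SD at month 3. Placebo adherence is 80%, active adherence 60% to 80%, and selection 0.3 to 1.0 log-odds per SD; all are assumed. Before any adjustment the bias runs from 0 to 1.06 points. The top value needs the strongest outcome link, 60% against 80% adherence, and selection twice as steep on the active arm. With 616 adherers per arm the SE is 15 × √(2/616) = 0.855, so 1.06 points is 1.24 SE. A nominal 2.5% test would then reject a true null in 15.9% of trials.

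**What adjustment does.** Simulation with no true effect, 3 points per SD of family score, and analysis of covariance on the baseline score as a stand-in for the longitudinal model:

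| Adherence, active v placebo | Selection, log-odds per SD | Unadjusted | Baseline score | Baseline and family score |
|---|---|---|---|---|
| 80% v 80% | 0.5 v 0.5 | about 0 | about 0 | about 0 |
| 70% v 80% | 0.5 v 0.5 | 0.13 | 0.11 | about 0 |
| 70% v 80% | 1.0 v 0.5 | 0.47 | 0.40 | 0.00 |
| 60% v 80% | 1.0 v 0.5 | 0.72 | 0.60 | 0.00 |

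In these scenarios the baseline score removes only about 15% of the bias. Adding the family score removes the rest, because here it is the only confounder and is fully measured.

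**The case against.** A reader might infer that the per-protocol estimate is confounded as it stands, that the plan overlooks the problem, or that the trial's conclusion is at risk. The documents do not support any of these.

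- **The bias is conditional.** That family circumstances drive adherence is not enough. They must act differently by arm, or adherence must differ by arm. Every child takes both a syrup and a sachet in identical packaging, and one 70% rule applies to all. The documents show no differential adherence. This stands, though blinding hides the allocation and cannot make tolerability equal; the Introduction itself says that iron may promote infection, including diarrhoea.
- **The plan has a companion estimate.** The CACE analysis in item 4 aims at the effect among compliers while keeping the randomised comparison, and does not require every driver of adherence to be measured. This stands. It does not correct item 3, however, and the plan does not say how the two are to be read together.
- **No decision rests on item 3.** The main analysis is intention-to-treat, and success is defined only by the primary null hypotheses at month 3. This stands in full.
- **Reusing the primary model is defensible.** With the covariates unchanged, a difference from the primary result reflects the change of population alone. This also stands, and is the reason to add a model and not replace one.
- **The size is assumed, and small beside the sampling error.** This holds for the two-group illustration. The second set of assumptions can exceed one SE, but only at its extreme.

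**Conclusion.** The point holds as a minor one. Item 3 conditions on adherence after randomisation and adjusts only for union and sex beyond the baseline score. If adherence or its drivers differ between arms, measured home and family differences can bias this sensitivity estimate. If the adherence process is the same in all arms, the bias is zero.

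Under the two-group assumptions the bias is about 0.1 to 0.7 points (central value 0.28), below one standard error of about 0.8. The more extreme continuous-score assumptions reach 1.06 points. None of these inputs comes from the documents, so the figures show what could happen and do not predict it. The intention-to-treat primary conclusion does not depend on item 3.

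**What to change.** In Sensitivity analyses, item 3:

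1. Keep the union-and-sex model, so that the per-protocol result stays comparable with the primary analysis.
2. Add a second model that also includes family care indicator and maternal education, each with a visit interaction. A main effect alone forces one slope at every visit, so a family association that changes between baseline and month 3 would be only partly adjusted for.
3. Allow other Table 1 variables if the blinded data review shows that they predict adherence.
4. State that the per-protocol contrast is not protected by randomisation, that the common-baseline-mean constraint need not hold among adherers, and that the result is to be read beside the CACE estimate.

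The cost is a few lines of SAP wording, one more model per outcome, and the handling of a few missing baseline covariate values. All the covariates are already collected. Under the SAP's own rule, tracked changes made before the code is broken still count as planned. The added model removes only measured confounding.
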